### Intervention

The tailored 12-week exercise interventions, possibly including a personalized diet advice or/and psychological counseling, will be designed based on the results of the baseline measurements for each disease group. Figure 2 shows this process and the content of the tailored exercise intervention. In order to design the tailored intervention a multidisciplinary team (the Rotterdam Exercise Team), consisting of a sports physician, treating medical doctor, physiotherapist, psychologist, dietician and the investigator ([name]) will compare baseline outcomes for each disease group to normal values of healthy peers in order to find possible limitations to physical activity. Based on these findings, the most fitting tailored intervention will be designed by the Rotterdam Exercise Team.

**Figure 2 F2:**
[figure not shown]
Design process and content of the tailored exercise intervention. MIP, Maximal inspiratory pressure; min, minutes; HIIT, high intensity interval training; HR, heart rate; VT2, ventilatory anaerobic threshold; REE, rest energy expenditure; kg, kilograms.

All children will participate in two or three supervised training sessions a week for 12 consecutive weeks. The most fitting form of physical exercise will be determined based on the consult with the sports physician in combination with the outcomes of the Maximal CPET, muscle strength measurements and core-stability measurements and measured maximal inspiratory pressure. Naturally, all previously published studies regarding exercise in the specific disease group will be taken in consideration when designing the tailored exercise intervention. When, for example, a certain training type has already been proven to be ineffective, this type of training will not be added to our tailored exercise intervention.

If a patient group shows a decreased PeakVO_2_ of <80% of predicted during baseline measurements, personalized aerobic training will be added to the exercise intervention consisting of 3 training sessions a week in heartrate zones: 2 (80–90% of HR at VT2) for 20 mins, 3 (90–95% of HR at VT2) for 3 × 5 mins and 4 (95–100% of HR at VT2) for 5 × 2 mins. If a patient group does not show a decreased PeakVO_2_ of <80% of predicted, personalized HIIT in heartrate zones 4 (95–100% of HR at VT2) and 5 (>100% of HR at VT2) will be added to the tailored intervention. Depending on measured muscle strength of the patient groups during the baseline measurements, muscle endurance exercises, high weight resistance exercises or body-weight and flexibility exercises, will be added to the program.

When a patient group shows decreased MIP (<80% of predicted), inspiratory muscle training (IMT) will be added using a Philips threshold IMT device following the previously published clinical guidelines of Hill et al. (26). Training will be given under supervision of a physiotherapist at a practice close to the children's homes. A researcher from the Erasmus MC—Sophia Children's Hospital will supervise all first training sessions and visit a training session of each patient every other week to monitor uniform execution of the tailored interventions. In addition, patients will be telephoned weekly to evaluate training progress (and if added, the dietary advice and psychological counseling) and assure compliance.

In addition to the physical training a personalized dietary advice and/or psychological counseling can be added to the exercise intervention if sought necessary by the Rotterdam Exercise Team.

A personalized dietary advice will be added if a patient group has insufficient intake, this will be determined based on the consult with the dietician, bodyweight and body composition measurements, the REE and the filled in food diaries. The personalized dietary advice will consist out of a healthy eating advice based on Dutch guidelines, including an advised calorie intake based on REE (27). A protein enriched diet of 2 g/kg daily will be added to the dietary advice when muscle endurance exercises or high-weight resistance exercises are included in the tailored exercise intervention.

Psychological counseling will be added to the personalized intervention if sought necessary by the psychologist, for example when fears regarding exercise are present in a disease group, cognitive behavioral therapy will be added. This will be determined based on the psychological consults with parents and children, the quality of life questionnaires, Tampa scale and the fatigue questionnaires.

### Outcome Measurements

#### Primary Study Outcome

Exercise capacity: Change in peak oxygen uptake (peak VO_2_), will be measured by maximal cardiopulmonary exercise testing (CPET).

#### Secondary Outcomes

Aerobic FitnessMaximal CPET: Oxygen exchange (VO_2_), oxygen consumption per heartbeat (O_2_pulse), ventilatory exchange (VE), load (W), heartrate (HR) and respiratory exchange rate (RER) determined at the ventilatory aerobic threshold (VAT) and at exhaustion (peak).Submaximal CPET: Average heartrate (HRavg) and maximum heartrate (HRmax).Six-Minute Walk Test (6MWT): Maximum walked distance in meters.Physical activity levels: Time in sedentary state and time in moderate activity will be measured using the ActiGraph GT3X accelerometer and structured interview.Health related quality of life: Will be measured using Child Health Questionnaires (CHQ-PF28 & CHQ-CF45).Fatigue: Will be measured by the Multidimensional Fatigue Scale questionnaire (PedsQolMFS).Fear of physical exercise: Will be measured using the TAMPA scale for kinesiophobia questionnaire and the kinesiophobia meter during the psychological consult.Muscle strength: Elbow flexion and extension, shoulder abduction, hip flexion and abduction, knee extension and flexion and squeezing strength will be measured using Hand-Held-Dynamometry (HHD).Core stability: Will be measured by time in seconds in balance for four core stability tests.Energy balance: Caloric intake estimated using a food diary, resting energy expenditure (REE) measured with indirect calorimetry.Body composition: BMI, body weight and body fat percentage, will be measured using both BOD POD and four side skinfold method.Lung function: Forced vital capacity (FVC), forced expiratory volume (FEV1) and FVC/FEV1 ratio will be measured using a spirometry tests.Effects on the following laboratory outcomes: IGF-1, CK, Growth hormone.

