### Randomization

Randomization will be performed in blocks of 4,6 using Castor. All children will be randomized in group A or group B. Group A will start with the tailored intervention after a control period of 6 weeks. Group B will start the tailored intervention immediately after the first measurement moment. Group A serves as controls for the whole group (with a 2:1 ratio) as group A does not have a washout period. Blinding of participants and physiotherapists to allocation is not possible due to the nature of the intervention.

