### Body Composition and Energy Balance

At each measurement moment patients the height, weight, and body composition, using a skinfold caliper (four skinfolds method) and air displacement plethysmography (ADP) on whole-body densitometry using the BOD POD (BOD POD body composition system, COSMED, Ltd, Concord, CA, USA) will be measured. Percent body fat (%BF) will be calculated using the equations published by Brook, Drunin, Rahaman and Wormsley et al. for the skinfold measurements, and the Lohman equation for the ADP (33–35).

All patients will keep up with a detailed food diary for three consecutive days and undergo an indirect calorimetry (Life Measurements, Inc, Concord, CA, USA), during the consult with the dietician to measure rest expenditure (REE). Measurements are performed after a fasting period of at least 2 h. Both measured REE and estimated REE, calculated using the Scholfield equation, are then converted to Total energy expenditure (TEE) (36–38).

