### Statistical Analysis

Data will be collected in the Castor online database. Patient characteristics will be described using descriptive statistics and tested for normality (using both the shapiro-wilk test and a visual evaluation of the histograms). A per protocol analysis will be used. Baseline characteristics between groups will be compared with the unpaired student's T-test for normally distributed data, Mann-Whitney U for not normally distributed data and Chi-squared test for proportions. Differences before and after the control or exercise period will be analyzed using a paired T-test for normally distributed data and Wilcoxon signed ranks test for not normally distributed data. If possible, missing outcome data will be imputed using multiple imputation. Statistical analyses will be performed using SPSS or R software. The significance level is determined at *P* < 0.05.

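### Body weight in growing children is tested against zero change over 12 weeks, so normal growth can be read as an intervention effect

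*Protocol article*

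**What the plan says.** - **Outcome.** Under Secondary Outcomes, body composition is given as "BMI, body weight and body fat percentage, will be measured using both BOD POD and four side skinfold method". The Study Population section sets the age range at 6–18 years.
- **Test.** Under Statistical Analysis: "Differences before and after the control or exercise period will be analyzed using a paired T-test for normally distributed data", with the Wilcoxon signed-rank test as the non-normal alternative. The only between-group tests described there are for baseline characteristics.
- **Periods.** Training lasts 12 weeks (Intervention). Under Randomization, "Group A will start with the tailored intervention after a control period of 6 weeks", while group B starts training at once and has no control period. The same section says "Group A serves as controls for the whole group (with a 2:1 ratio").
- **Standardised values.** For designing the intervention, the team will "compare baseline outcomes for each disease group to normal values of healthy peers". Peak VO2 and inspiratory pressure are judged as a percentage of predicted, for example "When a patient group shows decreased MIP (<80% of predicted"). No such scale is stated for change in weight.
- **Diet.** In the Intervention section: "A personalized dietary advice will be added if a patient group has insufficient intake". The advice includes an advised calorie intake.

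**The concern.** A paired test within the exercise period asks whether mean change differs from zero. A child who is still growing gains weight over 12 weeks with no intervention at all, so the test can reject for that reason alone.

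The control period looks as if it should guard against this, but it does not. The stated analysis does not compare the two periods. The control test also has half the expected growth and fewer children. Growth alone can therefore give a significant exercise period beside a non-significant control period, and a reader would naturally credit that pattern to training or diet. Where dietary advice was added for insufficient intake, weight gain is the hoped-for direction, so the bias would look like benefit.

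**Working it through.** **Inputs from the article.** The evaluable sizes per disease group are 21 (Fontan), 10 (BPD), 10 (Pompe) and 12 (IBD), from Sample Size Calculation. The exercise period is 12 weeks and the control period 6 weeks, in group A only. The significance level is 0.05, taken as two-sided.

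**Check of those sizes.** The paired normal approximation is n = ((1.960 + 0.842) × 2.19 / δ)², with δ equal to 5% of the baseline peak VO2:

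| Group | δ (ml/kg/min) | n computed | n stated |
|---|---|---|---|
| Fontan | 1.35 | 20.66 | 21 |
| BPD | 1.95 | 9.90 | 10 |
| Pompe | 1.885 | 10.59 | 10 |
| IBD | 1.80 | 11.62 | 12 |

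The stated sizes follow from a one-sample (paired) calculation, within one patient for Pompe. They are used below as the numbers analysed.

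**Assumptions, not in the article.** These are the annual weight gain without intervention, the SD of the weight change, and half of each disease group in group A (5, 6 and 10 children). The true intervention effect is set to zero.

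**Formula.** The expected change is annual gain × 12/52 for exercise and × 6/52 for control. The rejection probability is that of a two-sided one-sample t-test, from the noncentral t distribution with n − 1 degrees of freedom and noncentrality (shift / SD) × √n.

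**Mid case: 3 kg/year, SD 1.5 kg.** The shift is 3 × 12/52 = 0.69 kg. At n = 10 the noncentrality is 0.692 / 1.5 × √10 = 1.46, against a critical t of 2.26.

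| Scenario, exercise period | n = 10 | n = 12 | n = 21 |
|---|---|---|---|
| 0–1 kg/year, SD 1–2 | 5–10% | 5–11% | 5–17% |
| Half at 0.5 and half at 4 kg/year, SD 1.5 | 15% | 18% | 32% |
| 3 kg/year, SD 1.5 | 26% | 31% | 52% |
| 2–5 kg/year, SD 1–2 | 10–90% | 11–95% | 17–100% |

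At SD 1.5 the rate passes 10% at a growth of 1.5, 1.3 and 1.0 kg/year for the three sizes, and 20% at 2.6, 2.3 and 1.7 kg/year.

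**Control test, mid case.** The shift is 3 × 6/52 = 0.35 kg. With n = 5, 6 and 10 and the same SD of 1.5 kg, it rejects in 7%, 8% and 10%. If the SD shrinks with the square root of time (1.5 / √2 = 1.06 kg), the rates are 9%, 10% and 15%.

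**Exercise significant, control not.** By simulation (100,000 runs, SD 1.5 in both periods), growth alone gives this pattern in 24%, 29% and 47% when a group-A child's two changes are uncorrelated. Over correlations from −0.5 to 0.5 the ranges are 23–25%, 27–30% and 45–49%. With the smaller 6-week SD and no correlation the rates are about 23%, 28% and 44%.

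**If the two periods were compared directly.** An unscaled 12-week minus 6-week comparison still leaves 6 weeks of growth: 0.12 kg at 1 kg/year, 0.35 kg at 3 and 0.58 kg at 5.

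**BMI.** At an assumed 0.5 kg/m² per year and SD 0.6, the rates are about 8.5%, 9.4% and 13.4%, so BMI is only slightly affected.

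**The case against.** **The article is condensed.** It gives no unit for weight, and a full analysis plan may use standard deviation scores or an exercise-versus-control contrast; calling group A the controls suggests that one was intended. This carries some weight. But the article does name its test, lists body weight as an outcome beside BMI, and fixes the unequal periods. Applied as written, that rule produces the bias, so this is more than a missing detail.

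**The root problem is wider.** Testing within periods of unequal length, with no stated contrast, applies to every outcome, and standardised weight would still be tested against zero. That is true. For weight, though, the expected drift is known in direction, and standardising removes it as far as the group tracks the reference.

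**The size is assumed.** The rates run from 5% to 100% across scenarios, and holding the SD at 1.5 kg over 6 weeks slightly overstates the discordant pattern. Both points stand. They change the size of the bias, not its direction.

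**Apparent benefit is conditional.** No passage sets a desired direction for weight, and BMI is reported alongside. This also stands: the reading as benefit applies only where diet was added for insufficient intake.

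**Conclusion.** The concern holds. As written, the exercise-period test on body weight can reject because of growth alone, and the control period does not correct for it. Under a moderate assumed growth of 3 kg/year with SD 1.5 kg, the false rejection rate is 26–52% instead of 5%. In a slowly growing group it stays at 5–17%. The direction depends only on the children still growing; the size rests on assumed growth, SD and age mix. This is a minor correction to one secondary outcome. It does not affect the primary outcome or the sample size, and no claim is made about other outcomes.

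**What to change.** In Secondary Outcomes and Statistical Analysis, apply the planned tests to change in weight-for-age and BMI-for-age standard deviation scores, from a national reference by sex, and keep kg and kg/m² as description. Add a note that children with chronic disease may drift from the reference, so some bias can remain.

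The cost is one or two sentences and a reference-table conversion. Height and weight are already taken "At each measurement moment patients the height, weight, and body composition, using a skinfold caliper" among other methods, so no new measurements or patients are needed.

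The limit should be stated. If the group tracks the reference, the false rejection rate returns to 5%. The table shows what remains if it does not, for a reference gain of 3 kg/year and SD 1.5 kg (shift on SD scores, in kg-equivalents: (1 − fraction) × 3 × 12/52):

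| Group's gain as a fraction of reference | SD scores, n = 10 / 12 / 21 | Raw kg, n = 10 / 12 / 21 |
|---|---|---|
| Two-thirds | 7% / 8% / 10% | 14% / 16% / 27% |
| One-half | 10% / 11% / 17% | 10% / 11% / 17% |

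Below half of the reference gain, SD scores do worse than raw kg. The result also depends on the reference chosen, so it should be named in advance.

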#### Disease Specific Secondary Outcomes

For children with a Fontan circulation: An echocardiogram, magnetic resonance imaging and NT-pro-BNP measurement will be added to assess cardiac function.For children with BPD: Lung function will be measured before and after the maximal CPET.For Pompe patients: Muscle functioning using the Quick Motor Function Test (QMFT) and Supine To Stand Test (STST).For IBD patients: Effects on disease activity using the PCDAI and PUCAI scores and calprotectin will be measured in Feces. In addition to the CHQ, children will also fill in the Impact-III questionnaire to asses quality of life.

### Aerobic Fitness

Endurance will be assessed by maximal CPET, submaximal CPET, and 6-minute walking test (6MWT). All patients will undergo the maximal CPET, and submaximal CPET on the same electrically braked bicycle ergometer: Jaeger ER9000 (Viasys Healthcare, Hoechberg, Germany). The maximal CPET starts with 1 min of unloaded cycling with a rate of 60–80 repetitions per minute where after exercise intensity will be increased progressively until exhaustion (ramp protocol), the test ends with a 3 min recovery phase. The rate of increase will be considering the patient's functional capacities.

The submaximal CPET starts with 3 mins of unloaded cycling, followed by 6 mins of cycling with an exercise intensity set on half of the previously reached maximum workload during the maximal CPET, and ends with a 3-minute recovery phase. During both maximal and submaximal CPET, respiratory parameters and heart rhythm will continuously be measured using respectively breath by breath analyses: Oxycon Champion System (Viasys Healthcare, Conshohocken, United States) and 12 lead ECG. Blood pressure will be measured every 2 mins. Exercise tests with a peak respiratory exchange rate (RER) ≥ 1.00, a Heartrate >85% of calculated maximal heart rate and lung capacity <20% during the test will be considered maximal. The following parameters will be determined from the maximal CPET: Peak VO_2_ in ml/kg, peak minute ventilation (VEpeak), peak workload (Wpeak), peak heart rate (HRpeak), peak oxygen pulse (peakO_2_Pulse), peak RER, and ventilatory anaerobic threshold (VAT). The VAT will be assessed independently by two researchers using the ventilatory equivalents method. The following parameters will be determined from the submaximal CPET: average heart rate and HRpeak.

The 6MWT will be performed in accordance with the American Thoracic Society guidelines, however due to a lack of space the course will be 8 m of length instead of 30 m.

### Physical Activity Levels

During the consult with the Sports Physician, children and parents will be asked about the amount of time spend on physical activity a week. Subsequently, physical activity levels will be measured with a validated Actigraph GT3X+ accelerometer (firmware v3.2.1, ActiGraph Inc, Pensacola, FL, USA). The subjects will wear the accelerometer on their right hip for 2 week days and 1 weekend day. The actigraph will be removed only for swimming, showering, and sleeping. The Actigraph was set into tri-axial mode, using a 10-s epoch and 30 Hz. Non-wear time will be assessed using the Troiano protocol (28). Data will be analyzed with ActiLife® software (v6.10.2), counts per minute will be converted to metabolic equivalent (MET) using age specific formulas by Freedson et al. (29).

### Quality of Life, Fatigue, and Fear of Exercise

A semi-structured interview will be completed by a psychologist for both parents and children separately. In these interviews, biographical data, such as household composition, educational level, social participation, social-economic status, fear of exercise (answered by parents and children), perceived body image and quality of life (answered by parents and children) will be assessed.

The child health questionnaire (CHQ) child form (CF) and Parent form (PF) and the IMPACT-III questionnaire (for IBD patients) will be filled in at home and used to assess health-related quality of life (HRQol) (30). The PedsQL Multidimensional Fatigue Scale (MFS) CF and PF will be used to evaluate the effect of the exercise training on Fatigue (31). The TAMPA questionnaire and kinesiophobia questionnaire assess potential kinesiophobia (32).

### Core Stability and Muscle Strength

All muscle strength measurements will be performed in a standardized manner by the same trained investigator ([name]) using Hand-held Dynamometry (HHD). To assess core stability [name] measures time in balance for each of the following four core stability exercises: plank, back bridge, left side bridge, and right side bridge.

### Body Composition and Energy Balance

At each measurement moment patients the height, weight, and body composition, using a skinfold caliper (four skinfolds method) and air displacement plethysmography (ADP) on whole-body densitometry using the BOD POD (BOD POD body composition system, COSMED, Ltd, Concord, CA, USA) will be measured. Percent body fat (%BF) will be calculated using the equations published by Brook, Drunin, Rahaman and Wormsley et al. for the skinfold measurements, and the Lohman equation for the ADP (33–35).

All patients will keep up with a detailed food diary for three consecutive days and undergo an indirect calorimetry (Life Measurements, Inc, Concord, CA, USA), during the consult with the dietician to measure rest expenditure (REE). Measurements are performed after a fasting period of at least 2 h. Both measured REE and estimated REE, calculated using the Scholfield equation, are then converted to Total energy expenditure (TEE) (36–38).

### Lung Function

Forced vital capacity (FVC), forced expiratory volume (FEV1) and FVC/FEV1 ratio will be measured using an electronic spirometer (Masterscreen PFT; Carefusion; San Diego, CA) by a trained researcher.

### Laboratory Outcomes

At each measurement day blood samples will be collected from a peripheral vein and analyzed in the clinical laboratory of the Erasmus MC—Sophia Children's hospital, the following markers will be assessed in all patient groups: IGF-1, Creatine Kinase (CK), Growth hormone (GH). In addition, erythrocyte sedimentation rate (ESR), C-reactive protein (CRP) and albumin will also be assessed in IBD patients. In children with a Fontan circulation, N-terminal pro-brain natriuretic peptide (NT-proBNP) will be measured.

### IBD Specific Measurements

To assess the effects of the training program on disease activity: fecal calprotectin, lab measurements and PCDAI or PUCAI will be observed at each measurement moment. Remission is defined as PCDAI < 10 or PUCAI < 10, mild disease activity as PCDAI 10–27.5 and PUCAI 10–34, moderate disease activity as PCDAI 30–37.5 and PUCAI 35–64, severe disease activity is defined as PCDAI ≥ 40 and PUCAI ≥ 65 (39, 40).

### Pompe Disease Specific Measurements

In Pompe patients muscle function will be assessed using the Quick Motor Function Test (QMFT). The QMFT is a tool specifically constructed to measure motor function of Pompe disease patients (41). The test contains 16 motor function items that are specifically difficult for patients with Pompe disease and reflect daily life activities. Each item can be scored 0 (unable to perform) to 4 (can easily perform). Scores of each item are summed. The maximum score of 64 indicates normal muscle functioning. Additionally, the supine to stand test (STST) will be taken in order to assess the ability of a patient to rise from the floor. The STST measures the required time in seconds for a patient to move from a supine to standing position.

